**Methods:**

One hundred consecutive admissions to a binge eating treatment program were enrolled in the prospective single-arm trial between January 2019 and February 2020. Data were collected at admission, discharge, and 3, 6, and 12 months postdischarge, with admission, discharge, and 12-month follow-up as the major timepoints of interest. Results across the major timepoints will be analyzed with mixed effects general linear models.

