**Results:**

The primary aim is to assess the impact of the program on eating disordered behaviors at discharge and 12-month follow-up, which are hypothesized to improve as a result of treatment. Secondary hypotheses include improvements on comorbid symptoms, including trauma, depression, and obsessive-compulsive symptoms, as well as improvements on medical indicators of health, including cholesterol and triglycerides, at discharge and 12-month follow-up.

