In addition to interrupting eating disordered behavior, treatment also focuses on managing comorbid conditions, such as mood and anxiety disorders, and regulating sleep. Patients participate in daily group therapy based on a range of treatment modalities, including enhanced CBT (CBT-E) [16], DBT [17], ACT [18], narrative therapy, and exposure and response prevention, and on a range of topics, including body image, mood and anxiety, and nutrition. A primary focus on CBT-E and DBT was chosen because of the research evidence supporting their use for disorders characterized by binge eating. Trauma-informed care was also part of the treatment program. The average length of stay in the BETR program is 30 days, although this can vary considerably based on patients’ progress and insurance coverage.

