### A Priori Analytic Plan

All data at admission, discharge, and 3, 6, and 12 months postdischarge will be aggregated for the full sample and examined for patterns of missingness, outliers (>3 standard deviations from mean), and normality of distributions. Our a priori assumptions are that data will be missing at random, and all data will be normally distributed with the appropriately minimal proportion of outlier data points. Mixed models will be used to examine fixed and random effects of linear within-person change in BDI-II, EDQOL, OCI-R, STAI, RSE, DAS-SF, PCL-5, BES, and NEQ across our major timepoints of interest (admission, discharge, and 12-month follow-up). Mixed models will be run both unadjusted, as well as adjusted for person-level variables of BMI at admission, demographic variables of age, race/ethnicity, and gender, and diagnosis. Lastly, to examine the potential for different trajectories within-treatment and posttreatment, nested model comparisons will be conducted comparing the linear mixed models described above with mixed models including a quadratic time variable. Based on an expected effect size of at least *d*=0.5, and to account for a range of potentially inflated intraclass correlation coefficients that could reduce power, a sample size of 100 was determined to be sufficient to test both the mixed effects main effect hypotheses above, as well as the mixed effects 2-level interactions specified below.

All data at each of these timepoints will also be subset by patients above and below the threshold for history of trauma (defined as an ACES score ≥4) and above and below the most commonly established threshold for clinically significant levels of PTSD symptoms via the PCL-5 (PCL-5 ≥33) [48]. These subsets of patients will be compared using independent-samples *t* tests to determine any differences in point-prevalence of BDI-II, EDQOL, OCI-R, STAI, RSE, DAS-SF, BES, and NEQ by history of trauma or current trauma symptoms, and traditional moderation analyses with interaction terms added to the mixed models described above to determine any differences in changes over time of BDI-II, EDQOL, OCI-R, STAI, RSE, DAS-SF, BES, and NEQ by history of trauma or current trauma symptoms.

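### A single linear time trend over admission, discharge and 12 months does not estimate the change at discharge, and no rule makes the later quadratic model or the moderation tests do so

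*Protocol article*

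**What the plan says.** The Abstract (Results) states the target: "The primary aim is to assess the impact of the program on eating disordered behaviors at discharge and 12-month follow-up". Under Primary Hypotheses, a meaningful improvement is a change from before to after treatment of at least d = 0.5, and trauma history and current PTSD symptoms are expected to moderate the improvement.

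The A Priori Analytic Plan opens its modelling with "Mixed models will be used to examine fixed and random effects of linear within-person change" across admission, discharge and 12-month follow-up. As the last step for these models it adds nested comparisons, "comparing the linear mixed models described above with mixed models including a quadratic time variable", so that trajectories during and after treatment may differ. Moderation is tested by adding interaction terms to the mixed models, alongside t tests between the trauma and PTSD subsets at each timepoint.

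On timing, the Treatment section says "The average length of stay in the BETR program is 30 days, although this can vary considerably", and the Abstract (Methods) counts follow-up from discharge: "Data were collected at admission, discharge, and 3, 6, and 12 months postdischarge". The article does not state how time is coded.

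**The concern.** Treatment fills roughly the first month of a 13-month window. Most of the change should occur between the first two occasions, followed by maintenance or partial relapse. One slope cannot carry two separate quantities when the expected shape is a drop and then a plateau or rebound.

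If the lead model is what gets reported, the discharge effect is misstated, and with time in months so is the 12-month effect. The Discussion relies on prespecified hypotheses about the degree of improvement to offset the lack of a control group, so an estimator that distorts degree weakens that argument. The moderation hypotheses, listed among the primary ones, would inherit the same time term.

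**Working it through.** **Inputs from the article.** Three occasions; mean stay 30 days; follow-up counted from discharge, so about 0, 1 and 13 months; N = 100; threshold d = 0.5.

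**Assumptions.** The true mean patterns; unit SD at each occasion; equal within-person correlation ρ of 0.3 to 0.7; two-sided 5% tests; no dropout. Time is coded both in months (0, 1, 13) and by visit (0, 1, 2), because the coding is not stated.

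**The plan's own figure.** N = 100 is called sufficient for d = 0.5 without alpha, power or correlation, so it cannot be reproduced. For a simple admission-to-discharge contrast, d_z = 0.5/√(2(1−ρ)), which is 0.423 at ρ = 0.3 and 0.645 at ρ = 0.7. Power at N = 100 is then 98.8% to over 99.9%. The sample size is adequate for the main contrast; the question is whether the model tests that contrast.

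**Slope of the line.** With balanced data and a random intercept, the fixed slope is b = Σ(t−t̄)μ / Σ(t−t̄)².

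- Months: t̄ = 4.667; deviations −4.667, −3.667, 8.333; sum of squares 104.667. For true means 0, −1.0, −0.7: b = (3.667 − 5.833)/104.667 = −0.0207 per month. Fitted change: −0.0207 × 1 = −0.02 at discharge; −0.0207 × 13 = −0.27 at 12 months.
- Visits: deviations −1, 0, 1; sum of squares 2. The discharge mean has zero weight. b = −0.7/2 = −0.35, so the fitted changes are −0.35 and −0.70.

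| True change (discharge / 12 months) | Line, months | Line, visits |
|---|---|---|
| −1.0 / −0.7 | −0.02 / −0.27 | −0.35 / −0.70 |
| −0.8 / −0.4 | −0.004 / −0.05 | −0.20 / −0.40 |
| −0.5 / −0.5 | −0.02 / −0.29 | −0.25 / −0.50 |
| −0.8 / −0.8 | −0.04 / −0.46 | −0.40 / −0.80 |

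**Power of the month-coded slope test, N = 100.** SE = √((1−ρ)/(100 × 104.667)).

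- −0.8/−0.4: 8% to 11% by this formula for ρ 0.3 to 0.7. Simulated random-intercept fits give about 5%, because the misfit of the line inflates the residual variance.
- −1.0/−0.7: about 60% (ρ = 0.3), 72% (0.5) and 89% (0.7) in simulated random-intercept fits. The formula, which ignores the misfit, gives 72%, 85% and 97%.
- −0.8/−0.8: over 99%. The benefit is detected, but its size at discharge is understated.

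**The quadratic comparison.** Three parameters fit three means exactly. In the first two patterns the likelihood-ratio test prefers the quadratic model in essentially every simulated trial under either coding. For −0.5/−0.5 it does so with 98% to over 99% power (months) or 68% to 96% (visits).

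**Moderation.** Assume a moderator that reduces improvement by 0.5 SD at discharge and 0.25 SD at 12 months, two groups of 50, ρ = 0.5.

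- Linear-time interaction, months: slope difference (−3.667 × 0.5 + 8.333 × 0.25)/104.667 = 0.0024; SE = √(2 × 0.5/(50 × 104.667)) = 0.0138; z = 0.17; power about 5%.
- Linear-time interaction, visits: difference 0.125; SE = √(2 × 0.5/(50 × 2)) = 0.10; z = 1.25; power about 24% (23% simulated).
- Discharge contrast: difference 0.5; SE = √(2 × 2 × 0.5/50) = 0.20; z = 2.5; power about 70%.

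**The case against.** The strongest reply is that the remedy stands in the same paragraph. The quadratic comparison is planned precisely because the course may differ during and after treatment. With three occasions it is the categorical model of the means in another parameterisation, and both changes can be recovered from its coefficients. This stands. A reader might infer from the slope figures that the trial would miss a large benefit; the document does not support that, because it does not plan a linear-only analysis.

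Other parts of the reply also stand. The worst figures depend on month coding, which the article does not specify; visit coding recovers the 12-month change exactly. Nothing says that d will be computed from the slope. The phrase that attaches the interactions to the mixed models could cover the quadratic ones, and the subgroup t tests use no slope. A reader might also object that a random quadratic term cannot be identified from three occasions, but the article names only a quadratic time variable and plans no such random effect.

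It can further be said that coding and model-selection rules belong in a full analysis plan. That excuses their absence from the article. It does not excuse the stated choice of a linear lead model for an aim that names two timepoints, nor does the quadratic step say which model answers that aim.

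**Conclusion.** The point holds in a limited form and should be fixed. The lead model does not estimate the change at discharge under either time coding; with months it does not estimate the 12-month change either. In the assumed −1.0/−0.7 SD case the line returns between 2% (months) and 35% (visits) of the true discharge change. With month coding, its slope test has only about 5% to 11% power for a 0.8 SD benefit that is half lost by 12 months.

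The quadratic step makes it unlikely that a large main effect goes unnoticed. It leaves open which model supplies the two primary estimates. The larger exposure is moderation: if the interaction is with linear time, power for a difference concentrated at discharge falls from about 70% to about 5% (months) or 23% (visits). The gain applies to the discharge contrast; the 0.25 SD difference at 12 months has only about 24% power even as a contrast (0.25/0.20 = 1.25).

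The direction of these results follows from where the occasions lie. The sizes rest on the assumed mean patterns, correlations, equal groups and no dropout.

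**What to change.** Replace linear time with categorical time (admission, discharge, 12 months) and an unstructured within-person covariance. Name discharge minus admission and 12-month minus admission as the primary contrasts and the basis for the d ≥ 0.5 criterion. Use 12-month minus discharge for change after treatment, in place of the linear-versus-quadratic comparison. Test moderation as moderator-by-time on the same contrasts.

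Because discharge is defined by an event and length of stay varies, categorical occasions also remove the need to choose a time coding.

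The cost is wording in the analysis plan and one or two extra fixed effects per model, which is small with 100 patients. No further data are needed, and the article places the start of analysis after this plan.

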### Primary Hypotheses

It is hypothesized that meaningful improvements (defined here as pre- to posttreatment change with at least a medium Cohen *d* effect size of 0.5) will be demonstrated on measures of eating disorder psychopathology as a result of treatment addressing binge eating and other disordered eating behaviors. It is also hypothesized that a history of trauma and current posttraumatic stress disorder (PTSD) symptoms will moderate treatment effects, in that improvements in eating disorder symptoms will be less marked among those with a history of trauma or current PTSD symptoms. Although some studies have found that PTSD does not result in poorer treatment outcomes for binge eating [19,20], other studies have found that PTSD predicts more binge eating at end of treatment [21] and premature treatment dropout for patients with BN [22]. Given these mixed findings and the assumed increased level of severity in the current population seeking higher level of care treatment, PTSD will be examined as a moderator.

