### Secondary Hypotheses

It is also hypothesized that meaningful improvements will be demonstrated on a measure of experiential avoidance of weight-related feelings, thoughts, and actions, although no a priori hypotheses are made as to which subscales may improve the most. Depression, dysfunctional attitudes, and quality of life are also expected to meaningfully improve. Small improvements (defined here as pre- to posttreatment change with at least a small Cohen *d* effect size of 0.3) on a measure of obsessive-compulsive symptoms are expected, as addressing obsessive-compulsive symptoms is not a main target for treatment overall in the treatment program, but may be addressed in individual therapy. Anxiety and self-esteem are both hypothesized to meaningfully improve after treatment. Given that the treatment program incorporates trauma-informed care, it is hypothesized that meaningful improvements on a measure of PTSD symptoms will be found. It is also hypothesized that treatment will result in improved levels of triglycerides, high-density lipoprotein (HDL) and low-density lipoprotein (LDL) cholesterol, and glycated hemoglobin (HbA_1c_) due to normalization of eating patterns. It is well established that having a BMI over 30 shortens life and adversely impacts years of productive life [23]. The mechanism for those adverse effects is via contributors to the development of the metabolic syndrome and a heightened cardiac risk profile, such as hyperlipidemia and hyperglycemia. Thus, measuring those variables at baseline and then reassessing their serum values after treatment is one way to define the potential value of this program to reduce cardiac risk. Findings from this study may inform treatment guidelines for patients with BESD receiving treatment at higher levels of care.

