### Measures

#### Primary Outcomes: Eating Behavior

The Eating Pathology Symptoms Inventory (EPSI) [31] is a 45-item self-report measure of eating pathology with eight subscales: body dissatisfaction, binge eating, cognitive restraint, purging, restricting, excessive exercise, negative attitudes toward obesity, and muscle building. Items are scored on a 5-point scale from 0 (never) to 4 (very often). The EPSI has been shown to have good psychometric properties [32].

The Binge Eating Scale (BES) [33] is a 16-item self-report measure assessing binge eating behaviors that may be indicative of an eating disorder. It measures eating disordered behaviors as well as feelings associated with a binge episode. Items are measured on a 4-point scale, and the measure has been shown to have good psychometric properties [34].

The Night Eating Questionnaire (NEQ) [35] is a 14-item self-report measure of various aspects of night eating, including percentage of food consumed after dinner and frequency of nocturnal awakenings and ingestion of food. Items are scored on a 5-point scale.

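### EPSI, listed first among the three primary outcomes, and AAQW-R, a hypothesised secondary outcome, are in none of the analytic plan's outcome lists, so the primary hypotheses are tested only through BES and NEQ

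*Protocol article*

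**What the plan says.** Under Primary Outcomes: Eating Behavior, the article describes three instruments. EPSI comes first and "is a 45-item self-report measure of eating pathology with eight subscales". BES "is a 16-item self-report measure assessing binge eating behaviors that may be indicative of an eating disorder", and NEQ "is a 14-item self-report measure of various aspects of night eating". The first primary hypothesis is that improvements of at least d = 0.5 "will be demonstrated on measures of eating disorder psychopathology as a result of treatment addressing binge eating and other disordered eating behaviors". The second is that trauma history and current PTSD symptoms weaken the improvement in eating disorder symptoms. Neither hypothesis names an instrument.

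Under Secondary Hypotheses, "meaningful improvements will be demonstrated on a measure of experiential avoidance of weight-related feelings, thoughts, and actions". The measure in question is AAQW-R, which has three subscales. The authors decline to predict which subscale will improve most.

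Table 1 schedules both EPSI and AAQW-R at baseline, discharge, 6 months and 12 months.

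The A Priori Analytic Plan names its outcomes three times. The mixed models examine "linear within-person change in BDI-II, EDQOL, OCI-R, STAI, RSE, DAS-SF, PCL-5, BES, and NEQ across our major timepoints of interest". The t tests between trauma and PTSD subgroups use the same instruments without PCL-5. The moderation models use that shorter list again, "to determine any differences in changes over time of BDI-II, EDQOL, OCI-R, STAI, RSE, DAS-SF, BES, and NEQ by history of trauma".

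**The concern.** An instrument declared primary and collected four times would be expected to appear where the plan says what will be modelled. EPSI does not, while seven secondary instruments do. AAQW-R has a hypothesis of its own and is also absent.

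Two things are at stake. The first is coverage. BES addresses binge eating and NEQ night eating. Among the primary measures, only EPSI has subscales for purging, restricting, cognitive restraint, excessive exercise and body dissatisfaction. The program admits patients with bulimia nervosa, which the Background defines by compensatory behaviours, and the Treatment section names body image disturbance and compulsive exercise among the things treated. Followed literally, the plan tests none of these.

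The second is selection. The study has one arm, and the Discussion relies on a priori statements about the degree of improvement to offset the lack of a control group. An eight-subscale primary instrument with no assigned analysis leaves open which subscales will be presented once results are known.

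**Working it through.** This is a check of text against text. The plan gives no figure to reproduce on this point, and the stated sample size of 100 has no bearing on it.

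**Inputs.** The outcome roles come from the Measures section, the collection schedule from Table 1, and the three outcome lists from the A Priori Analytic Plan. Table 1 holds 11 questionnaires.

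| Questionnaire | Role | Mixed models | t tests | Moderation |
|---|---|---|---|---|
| EPSI | primary | no | no | no |
| BES | primary | yes | yes | yes |
| NEQ | primary | yes | yes | yes |
| AAQW-R | secondary | no | no | no |
| STAI | secondary | yes | yes | yes |
| BDI-II | secondary | yes | yes | yes |
| RSE | secondary | yes | yes | yes |
| OCI-R | secondary | yes | yes | yes |
| DAS-SF | secondary | yes | yes | yes |
| EDQOL | secondary | yes | yes | yes |
| PCL-5 | secondary | yes | no | no |

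**Counts.**
- Mixed models: 11 − 2 = 9 questionnaires. The two missing are exactly EPSI and AAQW-R.
- t tests and moderation: 9 − 1 = 8. The further absence is PCL-5, which is explained because PCL-5 defines one of the subgroups being compared.
- Primary instruments with a named analysis: 2 of 3.
- Secondary questionnaires in the mixed models: 7 of 8.

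**Could another sentence cover the two?** Three sentences are general enough to consider.
1. The opening of the analytic plan applies to all data, but only for screening of missingness, outliers and distributions.
2. The second paragraph subsets all data by trauma and PTSD status, but the tests that follow return to named instruments.
3. The abstract says that results at the major timepoints go into mixed models, and names no instrument.

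None of them assigns EPSI or AAQW-R a test.

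**What remains tested.** BES and NEQ are in the change models and in the moderation models. Each primary hypothesis therefore has a stated analysis for binge eating and for night eating, but none for the remaining EPSI domains.

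**The case against.** The strongest reply is that a journal article condenses a fuller plan, that the abstract promises mixed models in general terms, and that the lists are nowhere declared exhaustive. The hypothesised lipids and HbA1c are missing from the same lists, which points to incomplete drafting and not to a decision to drop EPSI. That may well explain the omission. It does not remove it. The lists name instruments one by one, three times, with no wording that marks them as examples, and the removal of PCL-5 from two of them suggests that they were composed with care. A document that declares a primary outcome and then leaves it out of every analysis it names is inconsistent with itself.

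Three stronger readings are tempting, and the document does not support them.

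- A reader might infer that the primary hypotheses cannot be answered at all. They can, in part: they name no instrument, and BES and NEQ are in all three lists. BES measures binge eating, which the eligibility criteria require as a predominant symptom.
- A reader might count eight EPSI subscales plus BES and NEQ and conclude that 8 of 10 primary scores are unanalysed. The article lists three primary instruments and nowhere makes each subscale a separate primary outcome. The supported figure is 1 of 3.
- A reader might treat the AAQW-R omission as weakening the primary hypotheses. AAQW-R is secondary and affects only its own hypothesis, which concerns the measure and makes no prediction by subscale.

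**Conclusion.** The point holds in a limited form. One of three primary outcomes (EPSI) and one hypothesised secondary outcome (AAQW-R) have no stated inferential analysis, although both are collected at four occasions. The primary hypotheses on change and on moderation are addressed only through BES and NEQ, so the conclusion they could support is narrower than the eating disorder psychopathology they refer to. The AAQW-R hypothesis is not addressed.

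This rests on reading the three lists as complete, which their form supports. It would fall away if a fuller analysis plan, dated before the analysis, already assigns both measures. Nothing here shows that the omission was intended or that selective reporting will occur, only that the plan as written does not prevent it for EPSI.

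**What to change.** Before analysis starts:

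1. Add EPSI to the mixed-model, t-test and moderation lists. State in advance which subscale or subscales bear on the primary hypotheses, and commit to reporting all eight. Which subscales those are is for the investigators to decide and justify; the document does not point to one.
2. Add AAQW-R to the mixed-model list, saying whether the total, the three subscales or both will be analysed.
3. If either omission was deliberate, say so, give the reason, and change the primary outcome list or the secondary hypothesis to match.

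No new data are needed: collection ended in May 2021 and analysis was expected from April 2022. The price is more models and more tests to report. If all subscales are used, the change analyses add (8 + 3) scores × 3 fits (unadjusted, adjusted, quadratic comparison) = 33 fits. EPSI moderation by the ACES and PCL-5 thresholds adds at least 8 × 2 = 16, and the t tests a further 8 × 2 = 16 at each timepoint. The larger number of tests is a reason to name the deciding subscales in advance.

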### Study Procedures

In addition to the standard admission and discharge questionnaires, and standard treatment described below, the 100 consecutive admissions for this study were asked to follow additional data collection procedures and were reimbursed accordingly. In addition to admission and discharge questionnaires, patients were asked to complete 6-month and 12-month follow-up self-report questionnaires. Patients were also asked to visit a laboratory facility at 3-month and 6-month follow-up to obtain a blood draw for a lipid panel (total cholesterol, HDL, LDL, triglycerides) and HbA_1c_. Participants received a US $25 Amazon gift card after completion of each of their admission and discharge assessments, and a US $100 Amazon gift card after the 6-month and 12-month follow-up intervals, for a possible total of US $250 in gift cards for completing all assessments.

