## Results

Recruitment of participants began in January 2019 and ended in February 2020. Data collection was completed in May 2021. Data analysis is expected to begin in April 2022, and results are expected to be published in fall 2022. The study was internally funded by ERC.

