## Discussion

### Principal Findings

The treatment program described in this study is unique in that it is developed specifically for, and solely treats, patients with BESD at the residential level of care. It is expected that this program, tailored to the needs of patients with BESD, will result in improvement in eating disorder psychopathology, comorbid mood and anxiety symptoms, quality of life, and improvement in physiological measures of health as a result of changes in eating disordered behaviors.

Several practical challenges in evaluating real-world treatment make it important to develop a protocol and explicitly state a priori intentions and expectations. First, the lack of a control group makes it difficult to assess a program’s effectiveness. Nevertheless, our a priori hypotheses on the *degree* of improvement may help findings from this study aid in the development of treatment guidelines for other programs seeking to help adults with BESD, which is critically important given the increased prevalence of BESD compared to other eating disorders, and the medical complications unique to BED [30]. Second, because treatment is not conditional on consenting to provide research data, potential bias from evaluating a program based solely on voluntarily collected research data over time may occur. To mitigate this bias in this study, we prospectively created a protocol that would allow for consecutive admissions to the program to be evaluated without the need for an additional research overlay that may lead to missing data in a biased fashion. Finally, because this is the first study to examine treatment for BESD at a higher level of care, it is important to clarify ahead of time exactly what treatment is being performed, what patients are admitted to the program, and what outcomes are expected as a result of treatment in the program.

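### The mixed models leave out the 6-month questionnaires, so 12-month loss that depends on the 6-month score can bias the 12-month change in either direction

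*Protocol article*

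**What the plan says.** - Collection (Study Procedures): beyond admission and discharge, "patients were asked to complete 6-month and 12-month follow-up self-report questionnaires". Table 1 marks all eleven listed questionnaires at baseline, discharge, 6 and 12 months. The Results section adds: "Data collection was completed in May 2021".
- Models (A Priori Analytic Plan): within-person change in nine named instruments is modelled "across our major timepoints of interest (admission, discharge, and 12-month follow-up". The abstract agrees: "Results across the major timepoints will be analyzed with mixed effects general linear models".
- Use of the 6-month wave (same section): "All data at admission, discharge, and 3, 6, and 12 months postdischarge will be aggregated for the full sample", then examined for missingness patterns, outliers and normality. No text brings this wave into a model or an imputation.
- Missing data (same section): "Our a priori assumptions are that data will be missing at random".
- Acknowledged risk (Principal Findings): "potential bias from evaluating a program based solely on voluntarily collected research data over time may occur". No direction is given for that bias.

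**The concern.** Missing at random means that, given the data the model sees, the chance of a missing value does not depend on the value itself. The assumption therefore belongs to a particular set of observed data. Suppose 12-month response depends on how a patient scored at 6 months. A model that includes the 6-month score treats this loss correctly. A model with only admission and discharge does not, because the 6-month score still predicts the 12-month score after those two are accounted for. The plan thus weakens its own assumption by leaving out the questionnaire wave closest to the 12-month endpoint.

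The stakes are moderate. The abstract makes 12 months one of the two timepoints of the primary aim. The trial is single-arm, so there is no comparison group in which attrition bias might partly cancel. The Principal Findings section rests the value of the study on the degree of improvement, and the Primary Hypotheses set the yardstick at d = 0.5 for pre- to posttreatment change. If that yardstick is also read at 12 months, a bias of 0.1 SD is a fifth of it (0.1 / 0.5 = 20%).

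**Working it through.** **The plan's own figure.** The article gives no figure for 12-month loss or its effect. Its only related figure is the sample size: "a sample size of 100 was determined to be sufficient" for d = 0.5. It cannot be strictly reproduced, because alpha, power and correlation are not stated. Assuming two-sided 0.05 and 80% power, a within-person change needs n = [√(2(1−ρ)) × (1.96 + 0.84) / 0.5]²:
- ρ = 0: (1.414 × 2.80 / 0.5)² ≈ 63
- ρ = 0.7: (0.775 × 2.80 / 0.5)² ≈ 19

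So 100 is ample for the main effect, and the matter here is chiefly bias.

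**Source of the bias.** Its size depends on two things: how strongly 12-month loss follows the 6-month score, and the slope of the 12-month score on the 6-month score once admission and discharge are in the model.
- Equal correlations of 0.5: slope = 0.5 / (1 + 2 × 0.5) = 0.25.
- Correlations falling with lag (admission with discharge, 6 and 12 months 0.50, 0.40, 0.35; discharge with 6 and 12 months 0.55, 0.45; 6 with 12 months 0.70): the normal equations give slopes of about 0.06, 0.07 and 0.64 for admission, discharge and 6 months. Check on the third equation: 0.4 × 0.06 + 0.55 × 0.07 + 0.64 ≈ 0.70.

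The second pattern should therefore give roughly two and a half times the bias of the first (0.64 / 0.25 ≈ 2.6).

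**Simulation.** All inputs except N = 100 are assumptions. Scores are in baseline SD units with higher meaning worse; means are 0, −0.9, −0.6 and −0.5, so the true 12-month change is −0.50. There are 600 trials per row, fitted by maximum likelihood with saturated means and unstructured covariance. Every simulated patient has a 6-month score. A negative bias means more apparent benefit.

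| 12-month loss depends on | Correlations | Loss | Bias, 3 occasions | Bias, 4 occasions |
|---|---|---|---|---|
| worse 6-month score, log-odds 0.5 to 1.0 | falling with lag | 20% | −0.05 to −0.08 | about 0 |
| same | falling with lag | 30% | −0.06 to −0.11 | about 0 |
| same | falling with lag | 40% | −0.08 to −0.15 | about 0 |
| same | all 0.5 | 20-40% | −0.02 to −0.05 | about 0 |
| better 6-month score, log-odds 1.0 | all 0.5 / falling with lag | 30% | +0.04 / +0.12 | about 0 |
| discharge score only | either | 30% | about 0 | about 0 |
| nothing (random) | either | 30% | about 0 | about 0 |

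With correlations falling with lag, improvement is overstated by 0.047 / 0.50 = 9% up to 0.145 / 0.50 = 29% when worse patients drop out.

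A second set of assumptions used a true change of −0.70, 35% loss, and a 12-month correlation of 0.75 with 6 months and 0.45 with discharge. Log-odds of 0.5, 1.0 and 1.5 gave three-occasion estimates of −0.784, −0.849 and −0.898, that is, overstatement by 0.08, 0.15 and 0.20 SD.

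**Covariance.** A random-intercept model with categorical time (30% loss, log-odds 1.0, correlations falling with lag) had a bias of −0.11 without the 6-month wave and −0.06 with it. Adding the wave removed only about half.

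**Precision.** Under the second set of assumptions the variance of the 12-month change is 9% to 14% larger without the 6-month wave, so the standard error is 4% to 7% larger (√1.09 = 1.04, √1.14 = 1.07). In the first set the loss is smaller: for random loss with correlations falling with lag, (0.126 / 0.124)² = 1.03. With equal correlations it is negligible.

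**Patients who miss both waves.** In the second setting at log-odds 1.0, the bias is −0.15 with three occasions. If half of those lost at 12 months also lack a 6-month score, the four-occasion model still carries about −0.06; at three quarters, about −0.10; if all do, −0.15.

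**The case against.** Naming discharge and 12 months in advance as the timepoints of interest is legitimate, and the article does keep the 6-month data for screening, including missingness patterns. Both points stand. Choosing the contrasts, however, does not require restricting the model to the same occasions.

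Three stronger readings are tempting, and the article supports none of them.
- **That the omission favours the program.** This needs patients who are worse at 6 months to be the ones lost at 12. The article gives no dropout rate or mechanism, and the bias it acknowledges has no stated direction. Zero or reversed bias is equally compatible with the text.
- **That adding the wave recovers the true value.** This holds only if patients lost at 12 months supplied 6-month scores and the covariance is flexible. The article says only that patients were asked to complete the questionnaires.
- **That a missing sensitivity analysis for data not missing at random is an error.** An article may leave this, like imputation detail, to the full plan.

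It is also fair to object that the bias figures come from models with categorical time, whereas the plan starts from linear change and compares it with a quadratic. The bias of the linear-time model was not computed. The argument about which data the assumption is conditional on applies to either form, but the figures show order of magnitude only.

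**Conclusion.** The point holds as a weakness in a stated analysis choice. The models are fixed to three occasions while a fourth is collected, and this makes the plan's missing-at-random assumption harder to meet than it need be. If 12-month loss depends on the 6-month score, the 12-month change can be biased by about 0.02 to 0.20 SD in the direction set by who drops out; if loss is random or depends only on the discharge score, the bias is zero. These sizes rest on assumed loss of 20-40%, log-odds of 0.5-1.5 per SD and the assumed correlations, none of which the article supplies. Confidence is high that the wave is left out and that the mechanism is real, and low on the sign and size in this trial. The change is worth making because it guards against bias in both directions at almost no cost.

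**What to change.** Fit the questionnaire mixed models to all four occasions (admission, discharge, 6 and 12 months), with time as a categorical factor and an unstructured or similarly flexible covariance rather than a random intercept alone. Keep the changes from admission to discharge and to 12 months as the contrasts of interest, so the stated major timepoints do not change. The linear-versus-quadratic comparison can stay as a secondary description; with four occasions a quadratic mean is no longer saturated, as it is with three.

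Report how many patients lost at 12 months supplied a 6-month score, since the gain applies only to them.

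The cost is one more mean and four more covariance parameters per outcome (4 × 5 / 2 = 10 against 3 × 4 / 2 = 6), plus a change of plan wording. No new data are needed: by the article's dates, collection ended in May 2021 and analysis was to begin in April 2022.
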